#### Statistical analysis

The test of hypothesis 1 compares the SMG and BOOK participants on the primary outcome (physical disability) and secondary outcomes (pain intensity, pain-related interference with activities, and depressive symptom severity) at each of the 3 follow-up assessments. The analytic method that we will use to evaluate this hypothesis is the mixed effects analysis of covariance (ANCOVA), as proposed by Laird and Ware [64] and implemented in the SAS PROC MIXED procedure [65,66]. This model will have two random effects, *site *and *person nested within site*. *Group *(i.e., treatment or control) and *Time *will be fixed effects. The repeated measurements of physical disability at post-intervention, 6 months, and 1 year will be the outcome measure. The baseline value of physical disability will be included in the model as a covariate. Any baseline variables that are correlated with the outcome variable and/or differ between the two treatment groups (e.g., gender, age, comorbidity) will also be included as covariates in the analysis. If the main effect for *group *is significant, contrasts within this model will be used to test for treatment effect separately at each of the three outcome times. Secondary analyses will be similar, fitting a mixed effects model that uses one of the secondary outcomes (e.g., pain intensity, pain-related interference, and depression) in place of physical disability. The analysis of Hypothesis 1 will be by intent-to-treat.

Hypothesis 2 involves comparing the SMG and BOOK groups on changes in process variables (pain-related beliefs and coping strategies). A mixed effects model, as described under hypothesis 1, will be used for these analyses. As for hypothesis 1, baseline variables that are predictive of outcome and/or differ between groups will be included as covariates in the analyses for hypothesis 2.

Hypothesis 3 involves the correlation of changes in beliefs and coping to changes in the outcome variables. For each assessment time, change from baseline will be computed and scatter plots will be used to describe relationships, with Pearson and/or Spearman correlation coefficients used to summarize the strength of the association. Although we hypothesize that significant associations in changes will occur only in the SMG group, we also will perform exploratory analyses in the BOOK group to assess for these associations.

In addition to performing major analyses to test study hypotheses, we will also perform exploratory analyses to examine whether there are subgroups of participants in whom the intervention had a particularly strong or a particularly weak effect. For example, we will explore whether: (1) there is a difference in response to therapy based on age group (young-old, mid-old, old-old); (2) men respond differently to therapy than women; and (3) pain severity at baseline is related to strength of treatment effect. These analyses will be performed using the ANCOVA described above, augmented by adding, for example, an indicator for female gender and the interaction term between gender and treatment group.

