#### Descriptive measures

The following measures are administered at baseline to describe the sample and to explore whether these variables are associated with treatment response. We will compare the two study groups on these measures to determine whether they are comparable at baseline.

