#### Outcome measures

##### Primary outcome

*Roland-Morris disability questionnaire (RMDQ): *The RMDQ [50] is widely used to assess physical disability associated with low back pain. The RMDQ has been demonstrated to be valid, reliable, and responsive to change [50-55]. Although developed as a measure of physical disability related to back pain, the RMDQ, re-worded without reference to the back, has been found to be a reliable and valid measure of physical disability for patients with other chronic pain problems as well [52]. The RMDQ is scored from 0–24, with higher scores indicating more severe physical disability. Physical disability, as measured by the RMDQ, is the primary study outcome.

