### Sample size calculations and statistical analyses

#### Power analysis/sample size calculations

A mixed effects model will be used to analyze data using the participant as the unit of analysis and controlling for baseline value of the outcome as a covariate. A reasonably accurate approximation to this analysis could be obtained by the following procedure: first compute change scores (pre to post) for each person, then collapse to get the mean change score within each site, then do t-tests on these means. This simpler model was used for power calculations, since it allows standard software to be used.

The plan to randomize by site, rather than by individual participant, required additional considerations in calculating statistical power. With this group-randomized design, power depends on the correlation of people within sites, or the *intra-class *correlation. Effect size is defined as the mean change score of all individuals in the intervention group minus the mean change score of all individuals in the control group, divided by the standard deviation of change score within groups. Power calculations for the proposed study are based on estimates of 34 sites (17 intervention and 17 control), 6.4 participants per site (N = 218) providing data at 12 months (20% attrition rate).

Table 3 shows how power (the probability of detecting a difference) varies with the correlation of individuals within site and the effect size. The second column of this table shows the "effective sample size," meaning that the study would have the same power as a study with this sample size and no clustering. If the correlation is zero, the effective sample size is 272, the actual sample size. A correlation of 1 would indicate that all individuals in each site have exactly the same outcome (i.e., no different from having one person per site), so the effective sample size would be 27. Analysis of data from a pilot study showed an intra-class correlation (ICC) of .07 [62]. Although this estimate should be interpreted cautiously because of the limited number of sites in the pilot study, it indicates that the intra-class correlation will probably be fairly small, perhaps 0.05 to 0.1. Our target sample size of 273 enrolled and 20% attrition at 12-month follow-up (yielding a final sample size of 218), assuming ICC=.1, will result in 84% power for detecting an effect size of .5, which Cohen [63] refers to as a "moderate" effect size.

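### The primary and Hypothesis 2 models take covariates from an open pool according to the observed data, partly because arms happen to differ at baseline

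*Protocol article*

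**What the plan says.** Under Statistical analysis, Hypothesis 1 is tested with a mixed-effects ANCOVA on the three follow-up measurements, with site and person within site as random effects. One covariate is fixed for the primary model: "The baseline value of physical disability will be included in the model as a covariate". The next sentence adds the selection rule: "Any baseline variables that are correlated with the outcome variable and/or differ between the two treatment groups (e.g., gender, age, comorbidity) will also be included". Secondary outcomes use a similar model. For Hypothesis 2 the article repeats the rule in its own sentence: "baseline variables that are predictive of outcome and/or differ between groups will be included as covariates in the analyses for hypothesis 2".

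Two other statements bear on this. Contrasts at the separate follow-up times are tested only if the group main effect is significant, so the covariate set affects that gate as well as the main result. Under Recruitment and randomization procedures, a facility is randomized only after all its participants have completed the baseline questionnaires.

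Under Descriptive measures the article also says: "We will compare the two study groups on these measures to determine whether they are comparable at baseline". It names no test or unit of analysis for that comparison.

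**The concern.** Gender, age and comorbidity are given only as examples. Nothing closes the candidate list, sets a cut-off for correlation or difference, or says which of the three follow-up times the correlation refers to. Two statisticians following the text faithfully could fit different primary models to the same data and obtain different p-values.

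The second criterion has a separate weakness. With allocation after baseline, any arm difference in a baseline variable arose by chance, and its presence says nothing about whether the variable predicts disability. A variable that is both imbalanced and prognostic would normally enter through the correlation criterion. What the imbalance criterion adds by itself is therefore mostly variables with no detectable relation to outcome. Being associated with arm, they cost some precision.

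At stake are the credibility of the primary p-value and, to a smaller degree, precision.

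**Working it through.** **1. The plan's own power figure.** Inputs from Power analysis/sample size calculations: "34 sites (17 intervention and 17 control), 6.4 participants per site (N = 218) providing data at 12 months (20% attrition rate"; "assuming ICC=.1, will result in 84% power for detecting an effect size of .5". Alpha is not stated; two-sided 0.05 is assumed.

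- Effective N = 218 / (1 + (6.4 − 1) × 0.1) = 218 / 1.54 = 141.6.
- Power = Φ(0.5 × √(141.6/4) − 1.96) = Φ(2.975 − 1.960) = Φ(1.015) = 0.845, against the stated 84%.
- Enrolment: 273 × 0.8 = 218.4.

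The figure reproduces. It comes from a t-test on site mean change scores, with no covariates beyond the change from baseline.

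**2. Size of the pool.** The Descriptive measures section yields about 12 candidates: age, race, ethnicity, gender, marital status, education, pain sites, pain duration, prior treatment, current treatment, MMSE and Charlson index. The process and outcome measures add about 18: two expectation ratings, self-efficacy, two CSQ subscales, nine CPCI subscales, pain knowledge, two BPI scores and GDS. As an illustration, if difference meant p < 0.05 in 12 valid independent tests, at least one variable would differ by chance in 1 − 0.95^12 = 46% of trials.

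**3. Cost of one non-prognostic covariate that just reaches p = 0.05 for imbalance.** Its R² with arm is t²/(t² + df), and the SE is multiplied by 1/√(1 − R²).

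- Participant-level variable (216 df): R² = 1.8%, SE × 1.009, power Φ(2.975/1.009 − 1.96) = 83.8%.
- Variable acting wholly at site level (32 df): R² = 11.5%, SE × 1.063, power about 80%.

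The listed measures are participant-level, so the first line is the relevant one and the second is an extreme.

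**4. Simulation of the rule.** 34 sites, N = 218, ICC 0.1, random-site model, t with 32 df; 6,000 null trials and 3,000 trials at effect size 0.5 per setting. Assumptions not in the article: 12 or 20 candidates, 3 of them prognostic (slope 0.25 SD each), covariate ICC 0.05, selection at p < 0.05 or p < 0.10, one outcome time. Ranges run over the four settings.

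| Covariates added | Type I error | Power at 0.5 |
|---|---|---|
| None | 4.3–5.3% | 83.4–84.4% |
| Three prognostic, fixed in advance | 4.4–5.2% | 88.5–89.8% |
| Correlated with outcome | 4.5–5.1% | 87.8–89.3% |
| Imbalanced only | 3.8–4.5% | 83.3–84.8% |
| Either criterion | 4.6–5.4% | 87.7–89.0% |
| Smallest p of none, correlated, imbalanced, either | 6.8–8.1% | – |

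Adding the imbalance criterion to the correlation criterion raised the SD of the treatment estimate in all 8 runs, by 0.7% (0.1539 v 0.1528) to 2.6% (0.1554 v 0.1514).

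**5. A second configuration.** 34 sites of 6, ICC 0.07, 12 candidates with 6 prognostic, slopes 0.15, 0.20 and 0.25, 2,500 null trials each. The SD under either criterion was 0.167, 0.167 and 0.165, against 0.167, 0.166 and 0.165 for the fixed prognostic set. Type I error under either criterion was 3.8–4.5%. In a further run with the same sites and ICC, taking the best of four readings (correlated, differing, either, both) gave 7.5%, against 5.4% for either criterion and 5.4% for a fixed list.

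**The case against.** The best defence is that the text is not as loose as it looks. The conjunction naturally means either criterion, and inclusion is mandatory. Applied that way by a fixed algorithm, the rule holds type I error and loses little power to a fixed set: 0.6 to 1.4 points in the simulation. That comparison even flatters the fixed set, which contained exactly the prognostic variables. A condensed article may also leave cut-offs, the follow-up time and blinded assessment of correlation to an unseen analysis plan.

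Most of this stands, and it limits the size of the point. It does not remove it. The article states the selection rule itself, and a plan that followed the rule would keep a data-dependent primary model and the imbalance criterion.

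Four stronger readings are tempting, and the documents do not support them:

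- *Selecting by imbalance loses substantial precision.* That holds for an imbalance-only rule, which the text does not state. Its power matches that of no extra covariates, so the shortfall comes from leaving prognostic variables out.
- *Type I error is inflated as a matter of course.* Inflation needs an analyst who chooses among readings after seeing results.
- *Baseline testing ignores clustering.* The article names no test, so a false-flag rate based on participant-level tests would rest on an assumed procedure.
- *Covariate sets that differ by outcome are an error.* Prognostic variables can legitimately differ between outcomes.

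**Conclusion.** The point holds as a modest pre-specification defect. The covariate set for the primary and Hypothesis 2 models depends on observed data and an open pool, and it affects both the main test and the gate to the time-point contrasts. Chance imbalance is a poor reason to adjust in a trial randomized after baseline.

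The imbalance criterion costs about 0–3% in standard error. Type I error stays near 5% if the rule is applied mechanically as either criterion; about 6–8% is a ceiling under selective choice of reading. These sizes rest on assumed numbers and strengths of prognostic covariates and on an assumed two-sided 5% level. The finding that the model is open does not depend on them.

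**What to change.** Replace the rule with a covariate list fixed before outcome data are examined: the baseline value of the outcome plus a short set of prognostic variables already collected. An example is age, gender, Charlson index, and baseline BPI pain intensity and GDS where these are not already the baseline outcome. Delete the between-arm difference criterion for both Hypothesis 1 and Hypothesis 2, and label any other adjustment a sensitivity analysis. The baseline comparison under Descriptive measures can stay as description but should not drive covariate choice.

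The cost is a small change of wording for the two hypotheses, a few participant-level degrees of freedom, and the possibility that an unexpected prognostic variable is left out of the primary model. The sensitivity analysis can show whether such an omission matters.

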### Study purpose and specific aims

The primary goal of this study is to evaluate the efficacy of a pain self-management group intervention (SMG), as compared with a control condition (BOOK), in decreasing physical disability, pain, pain-related interference with activities, and depression in older retirement community residents with chronic pain. In addition, we wish to determine the extent to which SMG participation is associated with changes in specific pain-related beliefs and coping strategies, and the extent to which changes in these process variables are associated with changes in outcomes (physical disability, pain intensity, pain-related interference with activities, and depression). We plan to test the following hypotheses:

*1. *At post-treatment and each follow-up, participants assigned to SMG, as compared with participants assigned to BOOK, will report less physical disability (primary outcome), and lower pain intensity, pain-related interference with activities, and depressive symptom severity (secondary outcomes).

*2. *Participants assigned to SMG, as compared with participants assigned to BOOK, will show greater pre- to post-treatment increases in self-efficacy and use of adaptive pain coping strategies and greater decreases in catastrophizing. Significant differences between SMG and BOOK groups in pain-related beliefs and coping strategies will be maintained at 6-month and 1-year follow-ups.

*3. *Pre- to post-treatment changes in specific pain-related beliefs (catastrophizing, self-efficacy) and coping strategies (Chronic Pain Coping Inventory subscales) will be associated significantly with changes in physical and social functioning, pain intensity, and depression over the same period among SMG participants. These changes in beliefs and coping strategies will be maintained at 6-month and 1-year follow-ups.

Figure 1 depicts the hypothesized relationships among study variables.

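### The Hypothesis 1 model lists Group and Time but no Group × Time term, so its three time-specific treatment contrasts are one and the same test

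*Protocol article*

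**What the plan says.** Hypothesis 1 (Study purpose and specific aims) is a claim about every assessment: "At post-treatment and each follow-up, participants assigned to SMG, as compared with participants assigned to BOOK, will report less physical disability (primary outcome").

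The Statistical analysis section sets out the model for testing it.

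- Random part: "This model will have two random effects", namely site and person nested within site.
- Fixed part: Group and Time are named as the fixed effects.
- Response: "The repeated measurements of physical disability at post-intervention, 6 months, and 1 year will be the outcome measure".
- Covariates: "The baseline value of physical disability will be included in the model as a covariate". Other baseline variables join it if they correlate with the outcome or differ between groups.
- Follow-on step: "If the main effect for *group *is significant", then "contrasts within this model will be used to test for treatment effect separately at each of the three outcome times".

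Secondary outcomes and Hypothesis 2 use the same kind of model. The only interactions mentioned anywhere are those for the exploratory subgroups, where the ANCOVA is "augmented by adding, for example, an indicator for female gender and the interaction term between gender and treatment group".

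**The concern.** The section specifies a model and then gives it a task that the model cannot perform. A treatment effect can differ between visits only if some term lets it, and neither the baseline score nor any other baseline covariate does so. An analyst who codes the listed terms and requests three contrasts will get the same answer three times.

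What is at stake is the each-follow-up part of Hypothesis 1. A benefit that has gone by 12 months would be reported as a 12-month benefit whenever the averaged effect is significant, and a strong early effect would be understated. A fading effect is conceivable here: the seven weekly sessions are followed only by booster calls, the last at 30 weeks after the final session. Hypothesis 2, which claims that differences in beliefs and coping are maintained at 6 months and 1 year, inherits the problem.

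**Working it through.** **1. The plan's own power figure.** Inputs from the Power analysis section: 34 sites, 6.4 participants per site, ICC 0.1, effect size 0.5. The significance level is not stated; two-sided 0.05 is assumed.

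- Effective sample size = 34 × 6.4 / (1 + (6.4 − 1) × 0.1) = 217.6 / 1.54 = 141.3. The plan's Table 3 gives 141.
- Standardised difference = 0.5 × √(141.3 / 4) = 2.97.
- Normal-approximation power = Φ(2.97 − 1.96) = 84.4%. With a noncentral t on 32 df (34 sites − 2) it is 82.2%.

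The stated 84% reproduces. It does not depend on the interaction term.

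**2. Algebra of the listed model.** For a participant with baseline score b at time t:

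E[Y] = μ + β·Group + τ(t) + γ·b + other baseline covariates.

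At fixed t, b and covariates, SMG minus BOOK is β, because τ(t), γ·b and the covariate terms cancel and the random intercepts have mean zero. This holds for each of the three times. The contrasts therefore have the same estimate, standard error and p-value as the Group effect. Once the gate on Group is passed, all three are passed.

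**3. Check on one simulated data set.** All inputs here are assumed: 34 sites, 5 to 8 people per site, site variance 0.1, person variance 0.5, residual variance 0.4, and true effects of −0.8, −0.4 and 0 at the three times (negative favours SMG).

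| Time | Group + Time: estimate (SE), z | With Group × Time: estimate (SE), z |
|---|---|---|
| Post | −0.605 (0.184), −3.28 | −0.983 (0.196), −5.00 |
| 6 months | −0.605 (0.184), −3.28 | −0.653 (0.196), −3.32 |
| 12 months | −0.605 (0.184), −3.28 | −0.181 (0.196), −0.92 |

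The additive estimate is the mean of the three separate ones: (−0.983 − 0.653 − 0.181) / 3 = −0.606, which agrees with −0.605 up to rounding.

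**4. Size at the planned sample.** Assumed: true effects 0.50, 0.25 and 0 SD; total variance 1; site effects constant over time (as in the listed model); complete data at 6.4 per site; within-person correlation 0.5 to 0.75.

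- Estimated effect at every time ≈ (0.50 + 0.25 + 0) / 3 = 0.25 SD. The bias is 0.25 − 0.50 = −0.25 SD at post-intervention and 0.25 − 0 = +0.25 SD at 12 months.
- Variance of the Group effect = (2 / 17) × (0.1 + w / 6.4), where w is the variance of one person's three-visit mean within a site.
- If the correlation r is taken within site, w = 0.9 × (1 + 2r) / 3.
  - r = 0.5: w = 0.60, SE = 0.151, noncentrality 0.25 / 0.151 = 1.66, probability of significance 36%.
  - r = 0.75: w = 0.75, SE = 0.160, noncentrality 1.56, probability 33%.
- If r is the total correlation, including the shared site effect, w = (0.9 + 2(r − 0.1)) / 3. The probabilities are 37% (r = 0.5) and 33% (r = 0.75).

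The critical value is t = 2.037 on 32 df. A 12-month effect that does not exist is thus declared in about 33–37% of trials.

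**The case against.** The strongest reply is that the wording implies the interaction. The section opens by comparing the groups at each of the three follow-ups, speaks of a main effect of group, and then asks for separate contrasts. That sequence makes sense only if Group × Time is in the model, so a competent statistician would add it. Because this is a journal article, the exact model statement may also sit in a fuller document. The subgroup sentence is weak evidence that the base model is additive, since it has to name whatever it adds.

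Much of this stands. The documents do not show that the trial team will run the additive model, and a reader should not infer that they will. But this is not a detail merely left out. The article lists the terms, points back to that list, and requires something of it that the list cannot deliver. Nothing elsewhere in the article repairs this.

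A reader might also infer that a constant site intercept makes the time-specific tests anti-conservative, and so ask for a site-by-time random effect, an unstructured within-person covariance or a particular degrees-of-freedom method. The documents do not support treating these as errors. They give no information on how site effects change over time, any share of site variance assigned to that would be a guess, and the contrasts are tested only after the Group effect passes its own test. These are modelling choices.

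**Conclusion.** The point holds as an inconsistency between the stated model and its stated use. Run as listed, the analysis tests one averaged group difference and reports it three times, so the each-follow-up claim of Hypothesis 1 is not tested. This conclusion is algebraic and needs no assumption about effect sizes.

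The size given, about 0.25 SD of bias in opposite directions at the first and last visits and a false 12-month claim in about 33–37% of trials, is only an illustration. It rests on an assumed decline from 0.50 through 0.25 to 0 SD, on the assumed correlations and test level, and on the additive model actually being run. The article gives no expected time course. If the true effect were constant over time, the identical contrasts would be unbiased.

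A reader might infer that the overall test of the primary outcome or the sample size is also compromised. The overall Group test remains a sensible test of the average effect over follow-up, and the stated power reproduces without reference to this term.

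**What to change.** Write the fixed part of the model as Group + Time (categorical) + Group × Time + baseline value + baseline covariates, and take the treatment contrasts at post-intervention, 6 months and 12 months from that model. State that the gating group effect is the treatment effect averaged over the three times; once an interaction is present, the Group coefficient alone depends on how Time is coded. Use the same form for the secondary outcomes and Hypothesis 2, with Time covering the visits at which each measure is collected.

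The cost is one sentence in the analysis section and, with three visits, two extra parameters. Sample size, stated power, visits and data collection stay as they are. If a fuller analysis plan already includes the term, the article's text need only be brought into line with it.

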### Recruitment and randomization procedures

Participants are recruited using newsletter announcements, flyers, brochures, and informational talks given at each facility. Retirement community residents who are interested in the study are screened to assess eligibility. Eligible residents who provide written informed consent are then asked to complete the baseline measures and to provide the name of their primary care provider (PCP), as well as permission to contact the PCP. PCPs of SMG group participants are sent a letter about the study and asked to contact the research nurse if there is any medical reason to restrict the resident's participation in the exercise portion of the study.

After all participants from a facility have completed the baseline questionnaires, the facility is randomized to receive either the BOOK or the SMG. Randomization is done by facility, rather than by individual participant, for several reasons. First, it expands the number of participating facilities by making feasible recruitment from smaller facilities. If approximately 5% of residents were recruited from any one facility, then it would not be scientifically or financially sound to involve facilities with fewer than 200 residents in independent or assisted living. A pilot study indicated that the ideal self-management group size is 5–12 participants. If we randomized within facilities, at least 10 participants would need to be recruited from each facility to allow 5 SMG participants. However, if all participants within a facility are randomized to the same condition, then smaller facilities can participate. If more than 12 residents in a facility randomized to the SMG condition enroll in the study, more than one group is scheduled. A second advantage of randomization by facility is that there is little risk of participants in one condition talking with participants randomized to another condition about their experiences in the study. Thus, there is less treatment contamination and likelihood that participants from different conditions will compare treatments, a situation that can provoke dissatisfaction among participants who do not receive the treatment of their choice.

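### Hypothesis 3 is judged by pooled correlations with no site term, although Hypotheses 1 and 2 model site; the effect on false positives is modest unless facility effects on coping and outcome are strongly shared

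*Protocol article*

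**What the plan says.** All places are in the Protocol article.

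- **Study purpose and specific aims** lists Hypothesis 3 among the hypotheses to be tested. It predicts that pre- to post-treatment changes in beliefs and coping "will be associated significantly with changes in physical and social functioning, pain intensity, and depression over the same period among SMG participants".
- **Statistical analysis**, Hypothesis 1: "This model will have two random effects", namely site and person nested within site. For Hypothesis 2: "A mixed effects model, as described under hypothesis 1, will be used for these analyses".
- **Statistical analysis**, Hypothesis 3: change from baseline is computed at each assessment and shown in scatter plots, "with Pearson and/or Spearman correlation coefficients used to summarize the strength of the association". No site or class term appears. The paragraph then refers again to significance: "Although we hypothesize that significant associations in changes will occur only in the SMG group".
- **Power analysis/sample size calculations** accepts that "power depends on the correlation of people within sites". It reports a pilot intra-class correlation (ICC) of .07 and expects .05 to .1.
- **Recruitment and randomization procedures**: "Randomization is done by facility, rather than by individual participant, for several reasons". SMG classes are run within facilities: "A pilot study indicated that the ideal self-management group size is 5–12 participants", and a facility with more than 12 enrolled runs more than one class.

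**The concern.** The section accounts for clustering in two of its three hypotheses and leaves it out of the third. SMG members of a facility share a class and a facilitator for seven weekly sessions, and the SMG facilitator also makes the booster calls. The sessions aim at both coping and disability. A class that goes well can therefore shift both measures for all its members.

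If that happens, the pooled coefficient contains a class-level component as well as any link between a participant's own change in coping and own change in outcome. An ordinary test of the coefficient also treats all participants as independent. A significant result would probably be read as participant-level evidence for the mechanism when part of it could be differences between classes.

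The exploratory comparison with BOOK would not expose this. BOOK has no classes, so an association driven by classes would appear in SMG only, which is the pattern the protocol predicts.

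**Working it through.** **Inputs.** From Power analysis/sample size calculations: 34 sites (17 SMG), 6.4 participants per site at 12 months, pilot ICC .07, expected range .05 to .1. SMG participants at 12 months: 17 × 6.4 ≈ 109.

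Assumptions, because the protocol gives no figure: two-sided 5% test; the same ICC for process change and outcome change; near-equal site sizes; no separate class effect within a facility; site-effect correlation between process and outcome varied from 0 to 1.

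**1. The plan's own figure (Hypothesis 1).** Effective N = 34 × 6.4 / [1 + (6.4 − 1) × .10] = 217.6 / 1.54 = 141.3 (Table 3: 141). Power at effect size .5 = Φ(.5 × √(141.3/4) − 1.96) = Φ(1.01) = 84.4%, against 84% stated. This reproduces and supports the two-sided 5% assumption. No figure is stated for Hypothesis 3.

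**2. What the pooled correlation estimates.** Let a share ICC of the variance of each change score come from site, let ρ_b be the correlation of the two site effects, and ρ_w the within-site correlation. Then

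pooled r = ρ_b × ICC + ρ_w × (1 − ICC).

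With ρ_w = 0 this is ρ_b × ICC: .025 at ICC .05 and ρ_b = .5; .07 at ICC .07 and ρ_b = 1; .10 at ICC .10 and ρ_b = 1.

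**3. Unrelated site effects.** The variance of r is inflated by about 1 + (m − 1) × ICC², with m = 109/17 = 6.41. That is 1.014, 1.027 and 1.054 at ICC .05, .07 and .10. The standard error rises by less than 3% (√1.054 = 1.027), so almost nothing is lost here.

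**4. False-positive rate by simulation.** Ordinary Pearson test, 17 sites, n = 109, no within-site association, 10,000 runs per cell:

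| ICC | ρ_b = 0 | ρ_b = .3 | ρ_b = .5 | ρ_b = 1 |
|---|---|---|---|---|
| .05 | 5.7% | 5.2% | 5.6% | 8.2% |
| .07 | 5.1% | 5.6% | 6.6% | 11.4% |
| .10 | 5.9% | 6.9% | 8.4% | 17.6% |

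Spearman is nearly the same. Repeat simulations put the ICC .05, ρ_b = 1 cell between about 8% and 9%. A rough check of the worst cell: the simulated mean r is .094 and its null standard error 1/√108 = .096, a shift of .98 standard errors. Φ(.98 − 1.96) + Φ(−.98 − 1.96) ≈ 16.5%, in line with 17.6%.

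**5. Larger n after treatment.** Hypothesis 3 mainly concerns pre- to post-treatment change, when fewer participants may have been lost. With 8 per site (n = 136) the ranges over ICC .05–.10 are 5.2–5.6% (ρ_b = 0), 5.6–9.2% (ρ_b = .5) and 8.6–19.8% (ρ_b = 1).

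**6. What the alternatives do.** A site-centred correlation rejects 4.7–5.5% across the cells in step 4. A mixed model with a random site effect and no centring rejects 4.7–5.9% for ρ_b from 0 to .5. Some excess remains if site effects are strongly shared.

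Power, by true within-site correlation ρ_w:

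| Setting | Pooled | Random site | Site-centred |
|---|---|---|---|
| ρ_w = .25, ρ_b = 0 | 66% | 69% | 69% |
| ρ_w = .25, ρ_b = .25 | 75% | 75% | 69% |
| ρ_w = .30, ρ_b = .30 | 89% | not computed | 84% |

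Centring therefore costs 75 − 69 = 6 or 89 − 84 = 5 points when site-level and person-level correlations are equal. The random-site model shows no loss in the two settings computed.

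**The case against.** **The harm is small within the plan's own ICC range.** This stands. At the pilot value of .07 and a site-effect correlation of .5 the rate is 6.6%. The double-digit rates need fully shared effects. A reader might infer that pooling makes false positives rise materially whatever the data; the documents do not support that.

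**The ICC is not tied to these variables.** This also stands. The protocol does not say which measure the .07 refers to and warns that the pilot had few sites. It gives no ICC for any belief or coping scale, and no site-level correlation between process and outcome.

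**A class-level shift may be part of what Hypothesis 3 means.** A reader might infer that only the within-site link is at issue and that any between-class association is an artefact. The aims section says only that changes will be associated among SMG participants, and SMG is a group treatment. The class component is spurious only for a participant-level claim. Site-mean centring should therefore not be imposed as the sole analysis. The question of the independent unit remains on either reading.

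**The article says only that coefficients summarize, and a fuller plan may attach proper inference.** This stands in part, since no p-value formula is given. But Hypothesis 3 is listed for testing and worded in terms of significance. Its stated method also differs from that for Hypotheses 1 and 2 in the same section, so this is a choice made in the text rather than a detail left out.

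**Conclusion.** The inconsistency is real. Site is modelled for Hypotheses 1 and 2 and dropped for Hypothesis 3, in a trial whose intervention is delivered by facility class. If facility or class effects move process and outcome together, the pooled coefficient mixes class-level and participant-level association.

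Over ICC .05–.10 at n = 109, the false-positive rate for a within-site association is about 5–6% with unrelated site effects and 5–9% at correlation .5. Only at the extreme of fully shared effects does it reach about 8–18%, with a spurious r of up to about .10. These figures rest on equal ICCs for both change scores and on a site-effect correlation that the documents do not give.

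This is a modest issue for a process hypothesis. It does not touch the primary outcome or the efficacy comparisons, which already model site.

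**What to change.** Base inference for Hypothesis 3 on a mixed model within SMG: outcome change regressed on process change, with a random site effect, and class within site where a facility runs more than one class. This follows the approach already chosen for Hypotheses 1 and 2. Keep the scatter plots and pooled Pearson or Spearman coefficients as description, and treat the exploratory BOOK analysis the same way, with site only.

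As a sensitivity analysis, report the within-site (site-mean-centred) association and the site-mean association separately, so that a reader can see how much of any result lies between classes.

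The cost is a change of analysis wording. The site identifier is already needed for the other hypotheses. The centred analysis uses 17 − 1 = 16 further degrees of freedom and can give up about 5 to 6 points of power if site-level and person-level correlations are equal. For that reason it should be the sensitivity analysis and not the main test.
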